### *Laboratory determinations*

Blood sampling will be performed at recruitment (T0) and at the end of the study (T6). Fasting peripheral venous blood samples will be taken at 8:30

[figure not shown]

## University of Naples “Federico II” - Naples, Italy

a.m. and immediately analyzed at the hospital laboratory of biochemistry for total cholesterol, HDL-cholesterol, LDL-cholesterol, triglycerides, insulin, and glucose. The HOMA-IR will be calculated as: the product of fasting glucose (mg/dl) and fasting insulin ( $\mu$ UI/ml) divided by 22.5.

To detect serum levels of ghrelin and IL-6 specific Human Ghrelin ELISA Kit (Biotechne, Minneapolis, USA) and IL-6 Human ELISA kit (Abcam, Cambridge, UK) will be used, with a detection limit of 9.38 pg/mL and 6.25 pg/ml, respectively.

Peripheral blood mononuclear cells (PBMCs) will be isolated from peripheral whole-blood (3ml) samples using the Ficoll-Paque (GE Healthcare, Uppsala, Sweden) method. For microRNA (miRNA) expression analysis, total RNA will be isolated from PBMCs using the TRIzol Reagent kit (Invitrogen, Carlsbad, CA, USA) and quantified with the NanoDrop 2000c spectrophotometer (Thermo Scientific, Waltham, MA, USA). RNA quality and integrity will be assessed with the Experion RNA Standard Sense kit (Bio-Rad, Hercules, CA, USA). Quantitative real-time PCR analysis of the miR-221 will be performed with the TaqMan miRNA assay kit and the TaqMan gene expression assay kit, respectively (both from Applied Biosystems, Grand Island, NY, USA) according to the manufacturer's instructions. Samples will run in duplicate at 95°C for 15 seconds and 60°C for 1 minute using an ABI Prism® 7900 Sequence Detection System (Applied Biosystems). Data analysis will be performed with the comparative threshold cycle (CT) method and expressed as  $2^{-\Delta\Delta C_T}$ .

[figure not shown]

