### **Secondary study outcomes**

- To evaluate glucose metabolism parameters (glycemia, insulinemia, HOMA Index), lipid metabolism parameters (total cholesterol, LDL, HDL and triglycerides), serum levels of the hormone ghrelin and of the proinflammatory cytokine IL-6, and on the expression of microRNA-221;
- To assess dietary and lifestyle habits;
- To assess metagenomic characteristic of the gut microbiota.

[figure not shown]

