## University of Naples “Federico II” - Naples, Italy

collected and reported in a specific clinical chart ([Annex 2.](#)).

The patients and their parents/tutor will be instructed on how to complete a food record ([Annex 3.](#)) for the evaluation of dietary patterns which will subsequently be analyzed by a specific software (Winfood - Medimatica Srl). Compliance with the recommendation regarding physical activity and sedentary behaviors at T6 was assessed by questioning about lifestyle habits ([Annex 4.](#)).

At enrollment (T0) and every month for 6 months (T1, T2, T3, T4, T5, T6) will be evaluated: body weight, height, BMI, weight for age percentile, height for age percentile, BMI for age percentile, waist circumference, blood pressure, eating behavior (3 days food record).

At the baseline (T0) and at the end of the study (T6) peripheral blood sampling will be performed for the evaluation of fasting blood glucose, basal insulin, HOMA-IR index, triglyceride, HDL cholesterol, LDL cholesterol, total cholesterol, ghrelin, and expression profile from PBMCs of miR-221. At enrollment (T0), before the start of interventions, and after 6 months (T6) a stool sample for each patient (3 g) will be collected for the metagenomic analyses of the gut microbiota. All samples will be collected from diapers in sterile plastic tubes and stored at -80°C until analysis.

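### The HOMA-IR formula pairs glucose in mg/dl with the divisor for mmol/l, so values computed as written are 18 times too high

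*Protocol*

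**What the plan says.** The protocol names HOMA-IR among its secondary outcomes: "To evaluate glucose metabolism parameters (glycemia, insulinemia, HOMA Index". The Study Design section places it at baseline (T0) and at the end of the study (T6), when "peripheral blood sampling will be performed for the evaluation of fasting blood glucose, basal insulin, HOMA-IR index" and the other blood measures.

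The formula appears once, under Laboratory determinations: "HOMA-IR will be calculated as: the product of fasting glucose (mg/dl) and fasting insulin", and the product is "UI/ml) divided by 22.5". Both units (mg/dl for glucose, micro-units per ml for insulin) and the divisor are therefore explicit.

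No other section converts glucose to mmol/l or gives a different divisor. The clinical chart in Annex 2 has a HOMA-index row, but with no unit and no formula. The sentence under Laboratory determinations is the only rule the trial has.

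**The concern.** HOMA-IR is a standard index with a fixed scale, and its constant depends on the glucose unit. The constant 22.5 goes with mmol/l, but the protocol uses it with mg/dl.

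Applied literally, the sentence puts the outcome on a scale that is not HOMA-IR. Group means, changes from T0 to T6, between-group differences and their confidence limits would all be inflated. A reader comparing them with published HOMA-IR values, or with any insulin-resistance threshold, would be misled.

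There is also a conditional risk. If someone notices the implausible size and corrects the calculation for some values only, for example at T6 but not at T0, a spurious 18-fold change appears in the data.

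**Working it through.** **Inputs from the protocol**
- Glucose unit: mg/dl (Laboratory determinations).
- Insulin unit: micro-units/ml (same sentence).
- Divisor: 22.5 (same sentence).

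**Inputs from outside the protocol**
- Definition of the index: the constant is the product of reference glucose 4.5 mmol/l and reference insulin 5 micro-units/ml, so that the reference subject scores 1. The protocol does not state this; it is the standard definition of the method.
- Molar mass of glucose: 180.16 g/mol, so 1 mmol/l = 18.016 mg/dl, conventionally 18.

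**Step 1. Where 22.5 comes from.** 4.5 x 5 = 22.5. The protocol's divisor is reproduced, but only with glucose in mmol/l.

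**Step 2. The divisor for mg/dl.** 22.5 x 18 = 405 (405.35 with the unrounded conversion). The protocol's pairing of mg/dl with 22.5 is not reproduced.

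**Step 3. Size of the error.** 405 / 22.5 = 18.0.

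**Step 4. Check at the reference point.** 4.5 mmol/l is 4.5 x 18 = 81 mg/dl. The index should equal 1. As written: 81 x 5 / 22.5 = 18. With 405: 81 x 5 / 405 = 1.

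**Step 5. Illustrative values.** The glucose and insulin figures are assumed; the protocol gives none.

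| Glucose (mg/dl) | Insulin (micro-units/ml) | As written (/22.5) | mg/dl with 405 | Ratio |
|---|---|---|---|---|
| 80 | 10 | 35.6 | 1.98 | 18.0 |
| 90 | 15 | 60.0 | 3.33 | 18.0 |
| 100 | 25 | 111.1 | 6.17 | 18.0 |

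Converting glucose to mmol/l and keeping 22.5 gives 1.97, 3.33 and 6.17 for the same rows, so the two consistent versions agree apart from the rounding of 18.016 to 18.

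**Step 6. Effect on a difference.** The gap between the first two rows is 60.0 - 35.6 = 24.4 as written. On the HOMA-IR scale it is 800/405 = 1.975 against 1350/405 = 3.333, a gap of 1.36. The ratio of the two rows is 1350/800 = 1.69 on either scale.

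**Step 7. Effect on the tests.** Multiplying all values by one constant leaves t statistics and ranks unchanged. In simulated skewed data with 27 per group, the Welch p-value was 0.238 and the Mann-Whitney p-value 0.035, both before and after multiplying by 18.

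**The case against.** No reading of the text rescues the formula, so the case on the other side concerns weight.

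- **The planned inference is safe.** The group comparisons under Statistical analysis give the same p-values on either scale. If HOMA-IR enters a regression as a covariate, its coefficient rescales but its test and the model fit do not. This stands.
- **Not every effect measure is affected.** Ratios, percent changes and standardised differences are unchanged. This also stands: the damage is confined to quantities in HOMA units.
- **No threshold is planned.** The protocol defines no HOMA-IR cut-off, responder outcome or subgroup. Misreading against a cut-off is therefore a risk in interpretation, not the failure of a planned analysis. This stands.
- **The error is recoverable.** Glucose and insulin are recorded separately, so HOMA-IR can be recomputed at any time. Nothing in eligibility, the primary outcome or the sample size depends on it. This is true, but recovery requires someone to notice and to depart from the written formula.
- **It may be a slip of the pen.** A value such as 60 would probably be questioned, and the unit or the divisor may simply have been mistyped. That is plausible, but nothing in the protocol shows which was intended.

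These points limit the consequences. They do not make the formula correct.

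**Conclusion.** The concern holds. As written, the formula yields values 18 times the HOMA-IR scale for every child at both T0 and T6. The conclusion rests on the standard definition of the index and the molar mass of glucose. The illustrative values show the size but do not affect the factor.

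Absolute values, mean changes, mean differences and confidence limits in HOMA units would be 18 times too large. Where HOMA-IR is a regression covariate, its coefficient per unit would be 18 times too small. Between-group p-values and relative measures are not affected, nor are the BMI z-score outcome and the sample size. It is a definite error in the definition of a named secondary outcome, and it should be corrected before any value is calculated or reported.

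**What to change.** Replace the sentence under Laboratory determinations with one of two equivalent versions:

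- HOMA-IR = fasting glucose (mg/dl) x fasting insulin (micro-units/ml) / 405; or
- HOMA-IR = fasting glucose (mmol/l) x fasting insulin (micro-units/ml) / 22.5, with mmol/l obtained as mg/dl divided by 18.

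State the chosen formula and units beside the HOMA-index row in Annex 2, and use it at T0 and T6 for every child. If any values have already been calculated, recompute them all from the recorded glucose and insulin rather than correcting some of them.

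The cost is one term in the protocol and in the calculation sheet. It needs no extra samples, visits, patients or budget.

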## University of Naples “Federico II” - Naples, Italy

delta CT. MiR-301b will be used as reference miRNA for data normalization.

Stool samples will be collected and immediately frozen at  $-80^{\circ}\text{C}$  at enrolment (T0) and at the end of the study (T6). DNA extraction from fecal samples will be carried out following the SOP 07 developed by the International Human Microbiome Standard Consortium ([www.microbiome-standards.org](http://www.microbiome-standards.org)). DNA libraries will be sequenced on Illumina NovaSeq platform, leading to 2x150bp, paired-end reads.

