### **Statistical analysis**

The Kolmogorov-Smirnov test will be used to determine whether variables will be normally distributed. For continuous variables the study groups will be compared using the mean equality test or, if necessary, the Mann-Whitney U test. The Kruskal-Wallis H-test will be used to compare the two groups. The comparison between two groups and between two samples will be performed using Welch's t test and Fisher's exact test respectively (with Bonferroni's correction). The  $\chi^2$  test and Fisher's exact test will be used for categorical variables. The data obtained will be assessed by means of linear logistic regression analysis in order to evaluate the possible influence of dietary factors and other variables (anthropometric data, glucose and lipid metabolism variables). We will use a generalized linear regression model (GLM) to examine the contribution of demographic, anamnestic and clinical data of children enrolled on the composition of the microbiota. A GLM model will be built and validated using the rms and ResourceSelection packages implemented in R respectively (<http://www.r-project.org/>). Multivariate statistical analysis (Analysis of the Main

[figure not shown]

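### miR-221 is put on the skewed 2^-ΔΔCT scale and compared by means; analysing ΔCT instead is a small, free gain for one secondary outcome

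*Protocol*

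**What the plan says.** The Protocol lists miR-221 among the secondary study outcomes ("and on the expression of microRNA-221"). It is measured twice: "Blood sampling will be performed at recruitment (T0) and at the end of the study (T6)".

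Laboratory determinations sets the scale: "Data analysis will be performed with the comparative threshold cycle (CT) method and expressed as" 2^-ΔΔCT. It also names the normaliser: "MiR-301b will be used as reference miRNA for data normalization". It does not name the calibrator for the second difference, and it mentions no analysis on the CT (log2) scale.

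The Statistical analysis section contains three relevant statements:
- Normality of each variable is screened with a Kolmogorov-Smirnov test.
- The test for continuous outcomes, with its fallback, is then given: "For continuous variables the study groups will be compared using the mean equality test or, if necessary, the Mann-Whitney U test".
- A further sentence names Welch's test without any condition: "The comparison between two groups and between two samples will be performed using Welch's t test and Fisher's exact test respectively".

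The same section also names Kruskal-Wallis for comparing the two groups. So a mean-based test is named twice. The rank-based route is partly conditional on the normality screen and partly stated without condition.

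**The concern.** CT values count doubling cycles, so they are already on a log2 scale, and differences between them are usually close to symmetric. Raising 2 to the power of minus that difference turns a symmetric quantity into a right-skewed one. Its arithmetic mean depends on the spread as well as on the centre.

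A test of means on that scale therefore has two weaknesses. A few large ratios inflate the variance and cost power. And if one arm is more variable than the other, the two means differ even when the typical change is the same. At stake is the reliability of one secondary laboratory outcome, for which the Protocol claims no power.

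**Working it through.** **Inputs from the Protocol.** 27 per group with 10% drop-out (Sample size): 27 × 0.9 = 24.3, so 24 evaluable per arm. Two-sided α = 0.05. No mean, SD, effect or power is stated for miR-221, so there is no planned figure to reproduce.

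**Assumptions.** ΔΔCT is normal, with SD 0.5, 1.0, 1.5 or 2.0 cycles. The true shift is 0.8 SD wherever power is quoted.

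**Step 1: shape of the ratio.** For X ~ N(0, SD²), the mean of 2^-X is exp[(ln 2 × SD)²/2]. At SD 1.0 this is exp(0.480/2) = 1.27. With w = exp[(ln 2 × SD)²], the skewness is (w + 2)√(w − 1).

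| SD (cycles) | Mean ratio, no change | Skewness |
|---|---|---|
| 0.5 | 1.06 | 1.1 |
| 1.0 | 1.27 | 2.8 |
| 1.5 | 1.72 | 6.9 |
| 2.0 | 2.61 | not computed |

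**Step 2: is the between-arm comparison biased?** With equal spread, both arms carry the same inflation and it cancels. In simulated null trials the mean difference between arms is about 0. Welch's test on the ratio rejects in roughly 3–5% of trials, which is nominal to conservative.

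**Step 3: power.** On the CT scale the noncentrality is 0.8 × √(24/2) = 2.77. The normal approximation gives Φ(2.77 − 1.96) = Φ(0.81) ≈ 79%; simulation with the t distribution gives 77%. The screened rule below applies an uncorrected Kolmogorov-Smirnov test with fitted mean and SD in each arm, then Mann-Whitney if either arm is flagged and Welch otherwise.

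| SD (cycles) | Welch on ΔΔCT | Welch on ratio | K-S flags at least one arm | Screened rule |
|---|---|---|---|---|
| 0.5 | 77% | 75% | 1% | 75% |
| 1.0 | 77% | 67% | 16% | 72% |
| 1.5 | 77% | 55% | 54% | 72% |
| 2.0 | 77% | 44% | 84% | 74–76% |

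The last cell is a range because separate simulation runs gave 74% and 76%. Mann-Whitney gives the same result on the ratio as on the CT scale, because ranks do not change under a log transformation. It loses only about 2–3 points.

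**Step 4: unequal spread, no shift.** With an assumed SD of 1.0 in one arm and 1.5 or 2.0 in the other, rejection rates against a nominal 5% are:
- Welch on the ratio: about 7–8% or 13–14%.
- Screened rule, uncorrected Kolmogorov-Smirnov: about 8% or 12%.
- Welch on the CT scale: about 5% in both cases.

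If the screen uses Lilliefors-corrected critical values, it flags skewness far more often. In a rerun of 20,000 trials with the same inputs, the screened rule then rejected in about 6% in both cases. The Protocol does not say which form it intends.

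**The case against.** The strongest objection is that the Statistical analysis section already protects this outcome. It checks normality and allows Mann-Whitney, which is unaffected by the log transformation. That largely stands: under the screen the power loss is about 1–6 points, against 2–33 for Welch on the ratio. Where skewness is severe, the screen usually catches it. It does not stand completely, because Welch's test is also named without the condition, and the uncorrected screen misses most trials at SD 1.0 or below.

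A second objection is that the laboratory section gives only a reporting format, and that the analysis scale belongs in a statistical analysis plan, which is not shown. That is fair and limits the weight of the point. Still, the Protocol does state a scale and a family of tests, and the two fit together poorly.

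A third is that nothing in the documents suggests unequal spread between arms, or an SD as large as 2.0 cycles. That also stands; those figures are illustrations.

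A reader might infer more: that because the mean ratio exceeds 1 when nothing has changed, the trial will show a false rise in miR-221. The documents do not support this. It would require each child's own T0 sample to be the calibrator and an arm's mean to be judged against 1, and the Protocol specifies neither. Under those two conditions, false upward calls would occur in about 7%, 18% and 25% of trials at SD 0.5, 1.0 and 1.5, against a nominal 2.5%. With a common calibrator and a paired T0–T6 test, rejection stays at 3.4–4.7%.

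**Conclusion.** The point holds as a minor one. The stated scale is a poor match for the stated mean-based tests, and ΔCT is better at no cost. With equal spread there is no false difference between the randomised arms.

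What remains is a power loss of about 1–6 points if the screen is followed. If Welch's test is applied directly to the ratio, the loss is about 2, 10, 22 and 33 points at SD 0.5, 1.0, 1.5 and 2.0 (77% minus 75%, 67%, 55% and 44%). There is also some excess false-positive risk if the arms differ in spread: about 8% or 12% in the assumed cases with an uncorrected screen, and less with a corrected one. All these sizes rest on assumed CT SDs, normal CT differences and 24 evaluable children per arm. The primary outcome is not affected.

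**What to change.** State that miR-221 is analysed as ΔCT (miR-221 minus miR-301b). Compare the arms at T6 by a linear model with T0 ΔCT as covariate. Back-transform the adjusted difference as 2^-(difference), with its 95% confidence limits, only to report a geometric-mean fold change. No calibrator is then needed for the test, because any common calibrator cancels from the between-arm difference. If 2^-ΔΔCT is still displayed, name its calibrator.

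The cost is a sentence or two of wording, settled before unblinding. The samples, assays and T0 values are already planned.

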## University of Naples “Federico II” - Naples, Italy

delta CT. MiR-301b will be used as reference miRNA for data normalization.

Stool samples will be collected and immediately frozen at  $-80^{\circ}\text{C}$  at enrolment (T0) and at the end of the study (T6). DNA extraction from fecal samples will be carried out following the SOP 07 developed by the International Human Microbiome Standard Consortium ([www.microbiome-standards.org](http://www.microbiome-standards.org)). DNA libraries will be sequenced on Illumina NovaSeq platform, leading to 2x150bp, paired-end reads.

### *Compliance and safety monitoring*

At each visit, the compliance to the allocated treatment will be assessed based on number of capsules unit left in the box. Compliance to the allocated treatment was defined as the consumption of 100% of the capsules. Furthermore, compliance with the recommendation regarding physical activity will be assessed by questions about daily exercises.

A dedicated phone number was available 7 days per week for parents/legal guardians of each patient in the case of occurrence of any suspected adverse event and at each monthly visit the safety will be monitored through a full clinical evaluation. Unscheduled visits will be performed if necessary.

[figure not shown]

## University of Naples “Federico II” - Naples, Italy

### **Sample size**

Considering a possible drop-out of 10%, will be required 27 patients per group (Group 1: n=27; Group 2: n=27) to observe a BMI z-score reduction at least of  $\geq 0.25$  after 6 months of intervention (Power of the study 90%; type 1 error =0.050, 2- tailed test).

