## **Aims**

### **Main study outcome**

- To determine the effectiveness on child weight status (BMI z-score reduction)

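### The named group tests use one BMI z-score value per child, so the 6-month comparison ignores the monthly data and, without imputation, omits any child with no T6 value; unequal, outcome-related loss could then bias it in either direction

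*Protocol*

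**What the plan says.** - **Outcome.** Under Main study outcome: "To determine the effectiveness on child weight status (BMI z-score reduction".
- **Sample size.** The trial is planned "to observe a BMI z-score reduction at least of" 0.25 after 6 months, with 90% power and "type 1 error =0.050, 2- tailed test". Loss is allowed for: "Considering a possible drop-out of 10%, will be required 27 patients per group". No SD is given.
- **Visits.** Study Design: "At enrollment (T0) and every month for 6 months (T1, T2, T3, T4, T5, T6) will be evaluated: body weight, height, BMI". Each child can therefore have up to seven BMI values, six of them after baseline.
- **Tests.** Statistical analysis: "For continuous variables the study groups will be compared using the mean equality test or, if necessary, the Mann-Whitney U test". The same section names the Kruskal-Wallis test and Welch's t test for comparing groups. Its regression models are aimed at the influence of dietary and other variables and at microbiota composition, not at BMI z-score over the visits.

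The protocol does not say that only completers are analysed, that early stoppers are excluded, or that a child who stops capsules is no longer followed.

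**The concern.** Each group test that the protocol names needs one number per child. With a 6-month target, that number is the change from T0 to T6. T0 enters through the subtraction but not as a covariate, and T1 to T5 do not enter the treatment comparison at all. A child who leaves after T3 has three post-baseline BMI values on file and, unless a T6 value is imputed, contributes none of them.

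In a weight trial, leaving may well be related to how the weight is going. If that happens more in one arm, the children with a T6 value are no longer comparable between arms. The monthly series records the child's course up to the point of leaving, which is the information needed to correct for this, and the named tests cannot use it. With 27 children per arm, a handful of uneven losses is enough to move the estimate.

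**Working it through.** **1. The plan's own figure.** The protocol states no SD, so 27 per group cannot be reproduced from its inputs. Only the drop-out step can be checked: 24 / (1 - 0.10) = 26.7, rounded up to 27, and in reverse 27 x 0.9 = 24.3. The size is consistent with about 24 children per arm with a 6-month value.

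**2. Implied SD (assumption).** If 0.25 is a between-group difference, 24 per arm and 90% power give, by the normal approximation, SD = 0.25 / [sqrt(2/24) x (1.960 + 1.282)] = 0.267. The t-based solution is 0.262.

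**3. Bias of a completers' comparison.** Let m_B and m_P be the shares lost on butyrate and placebo. Let D be how much worse the 6-month change is in children who leave than in those who stay, taken as equal in both arms. Each arm's completer mean is too favourable by m x D, so

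bias in (butyrate - placebo) = -(m_B - m_P) x D.

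For six children lost out of 54 (11%, close to the planned 10%):

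| Lost, butyrate / placebo | D = 0.10 | D = 0.25 | D = 0.50 |
|---|---|---|---|
| 3 / 3 | 0 | 0 | 0 |
| 5 / 1 | -0.015 | -0.037 | -0.074 |
| 1 / 5 | +0.015 | +0.037 | +0.074 |
| 6 / 0 | -0.022 | -0.056 | -0.111 |
| 0 / 6 | +0.022 | +0.056 | +0.111 |

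Example: (5/27 - 1/27) x 0.25 = 0.037. A negative sign overstates the butyrate effect and a positive sign understates it. Against 0.25, the non-zero entries run from 6% (0.015) to 44% (0.111).

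**4. Simulation.** All inputs are assumptions: SD of 6-month change 0.262, random slopes plus measurement noise of 0.08, true effect -0.25, and drop-out after T3 more likely with a worse observed T3 change (log-odds 1.5 per SD).

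| Loss, butyrate / placebo | Completers at T6 | Using the visits before drop-out |
|---|---|---|
| 15% / 5% | about -0.275 | about -0.25 |
| 18.5% / 3.7% (5 v 1 of 27) | -0.284 | about -0.25 |
| 5% / 15% | about -0.228 | about -0.25 |
| 10% / 10% | about -0.25 | about -0.25 |

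Repeat runs moved the 15%/5% figure between -0.273 and -0.275. The simulated D was about 0.25, so step 3 predicts -(0.15 - 0.05) x 0.25 = -0.025, in agreement.

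With no true effect, completers show about -0.023 at 15%/5% and about -0.033 at 18.5%/3.7%. Welch's test then rejects in 5.8% and 6.8% of 4,000 trials instead of 5% (simulation error about 0.34 points).

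**5. Scale.** The standard error of the difference with 24 per arm is 0.262 x sqrt(2/24) = 0.076. A shift of 0.025 is about a third of it, and 0.034 about 0.45 of it.

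**6. Power.** At SD 0.267, power is 0.90 with 24 per arm and 0.93 with 27. The loss of at most 3 points is already inside the stated 90%.

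**The case against.** **The 10% allowance is not a decision to discard children.** This stands. Enlarging a sample for expected loss protects power and is just as normal beside an intention-to-treat analysis. A reader might infer from Sample size that drop-outs are to be left out of the analysis. The text defines no analysis set.

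**Exclusion is inferred.** This also stands. Analysis population and missing-data rules commonly sit in a SAP, and none is shown, so their absence is no finding. What remains is the choice that the protocol does make: tests with one value per child for an outcome measured at seven visits. An imputation rule could supply a T6 value, but the tests themselves still take no account of the monthly course.

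**Stopping capsules is not leaving follow-up.** It is tempting to say that every child who stops early disappears from the result. The visit schedule carries no condition on taking capsules, so a child who stops them and attends T6 has a value and enters every named test.

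**The direction of bias is open.** A reader might infer that butyrate would be favoured. That needs more loss of poor responders on butyrate, and the protocol gives no drop-out or tolerability data by arm. If one common rule makes poor responders leave and butyrate works, placebo loses more: with 10% total loss the split was 5.6%/14.4% and completers gave -0.230, an understatement.

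**The simulation suits the remedy.** True: drop-out was made to depend only on observed T3 values, which is what a likelihood-based repeated-measures model assumes. It shows what the monthly data can recover in that case, not in every case.

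**A single 6-month endpoint is legitimate, and six visits with 54 children is thin for an unstructured covariance (21 parameters).** Both points are fair. The remedy keeps the 6-month contrast and needs a fallback covariance structure.

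**Conclusion.** The point holds as an improvement to the stated analysis, not as an error in the sample size. The named group tests make no use of the T1 to T5 BMI data or of T0 as a covariate, and without imputation they omit children who have no T6 value.

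The consequence is conditional. Loss must be unequal between arms (or selective in different ways) and also related to outcome. At about the planned 10% total loss, the assumed 15%/5% and 5%/15% splits move a true -0.25 to about -0.275 or -0.228, roughly 10% either way, and an equal split leaves it unbiased. The wider range of 0.015 to 0.111 z-score units rests on assumed values of D and on splits as uneven as 6 to 0. The SD is back-solved from the sample size, not stated. The documents do not support saying that the trial will be biased, or that it will favour butyrate.

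**What to change.** Make the primary analysis a mixed model for repeated measures on BMI z-score change at T1 to T6, in all randomised children as assigned. Include arm, visit, arm by visit and T0 BMI z-score. Use small-sample degrees of freedom, and name in advance a simpler covariance structure to be used if the unstructured one does not converge. Report the arm difference at T6 as the result, and keep the two-sample comparison at T6 as a sensitivity analysis.

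This costs a change of wording and a little more analysis work. It needs no extra children, visits or measurements. Its limit should be stated with it: the correction holds only if missingness depends on observed data.
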